**C.2.1.2 Aim 2 major endpoints**

Similar to Aim 1, the primary endpoint will be based on Nugent criteria; BV free survival will be defined as Nugent score < 7. Data will be analyzed in an intent-to-treat manner comparing survival without BV three-months after treatment for those assigned to the diaphragm/Replens arm vs. the non-intervention arm.

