Use of the diaphragm with nonoxynol-9 (N9) based spermicide has been associated with altered vaginal bacterial microflora including decrease rates of lactobacillus colonization 11. However, most regard the alteration of vaginal flora and increased risk of urinary tract infection a direct result of the N-9 spermicide and not related to the diaphragm alone 12. Importantly, Buffergel a microbicide with the ability to maintain a low vaginal pH was associated with profound reductions in BV after a short period of use 13. Therefore, we propose to study the effect of the diaphragm used with Replens (a commercially available vaginal lubricant with pH buffering capacity) on the vaginal flora and on the rate of BV in women enrolled in a randomized controlled trial.

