**B. The Specific Aims**

**Specific Aim 1:** To compare rates of BV in women in the diaphragm with Replens with those of women in the condom only arm.

- 1. To compare Nugent’s scores in the 2 arms as the full 10 point scoring system during a 12 – 24 month follow-up after randomization, and
  2. To assess the influence of the intervention on vaginal colonization by *Lactobacillus spp*. as note on Gram stain.

**Specific Aim 2:** To determine whether women in the diaphragm used with Replens arm have an altered rate of recurrence after treatment of BV compared to women in the condom only arm.

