**C. Methods**

**C.1 Overview**

At the Zimbabwe site, self-collected vaginal swabs will be collected on the 500 women enrolled in the RCT at their enrollment visit and every three months per study protocol. Data on recent vaginal hygiene and other practices that may affect vaginal microflora will be collected on an additional questionnaire at every follow-up visit. Since the site will enroll over 2,000 women over the course of the randomized trial, enrollment for the BV component will take place at one of the three recruitment centers, and will be closed once the full sample size has been attained.

To study Aim II, 500 women with symptomatic BV will be required. Unfortunately, since we will not be able to perform vaginal Gram stains in real-time, the initial diagnosis of BV will be made using the modified Amsel’s criteria (pH > 4.7, positive whiff test and clue cells on wet mount). Those diagnosed with BV will receive a 5-day course of metronidazole 400 mg three times per day. Vaginal Gram stains will also be collected. Only women with a Nugent score  7 and with 3 of 3 Amsel’s criteria will be analyzed. Women enrolled in Aim II will have a vaginal Gram stain repeated on a self-collected vaginal swab three months after treatment. The prevalence of BV after three months will serve as the primary endpoint for this aim.

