**C.2.2.3 Aim 2 sample size**

We assume that a minimum 5% of participants will present with symptomatic BV at every visit. Given the projected sample of 2200 women for the Zimbabwe (and a total of nearly 13,000 follow-up visits), this implies that approximately 660 diagnosed cases of symptomatic BV should be observed. The primary outcome for this aim will be recurrence of BV within three months following treatment for symptomatic disease. We assume that recurrence rates will be compared across arms on an intent-to-treat basis using a chi-squared statistic, and that loss-to-follow up rates in a three month visit cycle will not exceed 5%. Given these assumptions, and assuming three-month recurrence rates among women receiving only condoms in the range 0.1 - 0.2, a total sample size of 500 women will provide 80% power to detect a 33% reduction in recurrence associated with treatment at the 5% significance level.

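### BV sub-study Aim 2 is labelled intent-to-treat, but its analysed set is formed mainly after randomisation, so randomisation does not protect the recurrence comparison

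*Protocol*

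**What the plan says.** All references are to the protocol; the sub-study is Appendix 16.1.

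- **Question.** Section B asks whether women in the diaphragm arm "have an altered rate of recurrence after treatment of BV compared to women in the condom only arm".
- **Label.** C.2.1.2 states: "Data will be analyzed in an intent-to-treat manner comparing survival without BV three-months after treatment for those assigned to the diaphragm/Replens arm". C.2.2.3 repeats the intent-to-treat label.
- **Who is analysed.** C.1 makes the diagnosis on modified Amsel criteria ("pH > 4.7, positive whiff test and clue cells on wet mount"). Diagnosed women are treated, and the analysis is limited to those with a high Nugent score "with 3 of 3 Amsel’s criteria will be analyzed".
- **When cases arise.** C.2.2.3 assumes that at least 5% of participants present with symptomatic BV at each visit, and applies this to 2,200 women "and a total of nearly 13,000 follow-up visits" to obtain about 660 cases, of which 500 women are needed.
- **Test.** C.2.2.4 compares recurrence proportions between arms with a chi-squared test. No adjustment is mentioned.
- **What the intervention may do.** Section A describes the gel as "Replens (a commercially available vaginal lubricant with pH buffering capacity", and section 4.4 of the main protocol also refers to its buffering action. Aim 1 (C.2.2.1) is powered for a 25% difference in BV prevalence between arms, a relative risk of 0.75.
- **Definition of intent-to-treat.** Section 12.7 defines that set as every eligible woman who was randomised, and gives intact randomisation as its merit.

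**The concern.** An intent-to-treat comparison is unconfounded because membership of the analysed set is settled before treatment can influence it. In Aim 2 a woman joins the set by developing symptoms, being diagnosed, being treated and being confirmed on Gram stain, and in most cases this happens while one arm is using the diaphragm and gel. If the products change how often BV occurs, which cases become symptomatic, or how often the pH criterion is met, then the women entering from the two arms can differ in their underlying tendency to recur. A difference in recurrence may then reflect who entered and not what the products did.

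At stake is the claim attached to the result. As written, the comparison would be reported with the authority of a randomised one, although nothing planned corrects for selection, or would even reveal it.

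**Working it through.** **1. The plan's case count.** With 2,200 women, an average of six follow-up visits and 5% per visit: 2,200 × 6 = 13,200 visits, and 13,200 × 0.05 = 660 cases. This reproduces the stated figure using follow-up visits only. No enrolment cases are in it.

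**2. How many could enter before randomisation.** C.1 does not expressly exclude BV diagnosed at enrolment, and section 9.4 lists assessment and treatment of reproductive tract infections ahead of randomisation. At the 5% minimum rate this gives at most 2,200 × 0.05 = 110 women, leaving 500 − 110 = 390 who must enter afterwards. A higher symptomatic rate at enrolment would raise the 110.

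**3. Label against definition.** Section 12.7 requires every eligible randomised woman. Aim 2 analyses a subset fixed by later events. Both cannot be called intent-to-treat in the same protocol.

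**4. Illustration of possible bias, with no true effect on recurrence.** The documents give no entry rates by arm, so these are assumptions:

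- Control entrants are half high-risk and half low-risk for recurrence; the high type has q = 2 to 4 times the risk of the low type.
- The intervention halves entry in one type only. Overall entry is then (0.5 + 1)/2 = 0.75 of control, the value borrowed from Aim 1. The 500 women split 500/1.75 ≈ 286 control to 214 diaphragm.
- Control recurrence is 0.1 to 0.2, from C.2.2.3.

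With s the high-risk share among diaphragm-arm entrants, RR = [s·q + (1 − s)] / [(q + 1)/2].

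| Entry halved in | s | RR, q = 2 | RR, q = 4 |
| --- | --- | --- | --- |
| low-risk type | 0.5/0.75 = 0.667 | 1.667/1.5 = 1.11 | 3.0/2.5 = 1.20 |
| high-risk type | 0.25/0.75 = 0.333 | 1.333/1.5 = 0.89 | 2.0/2.5 = 0.80 |

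By normal approximation to the two-sided chi-squared test, the nominal 5% test rejects in about 7-12% of trials at control recurrence 0.1 and about 9-20% at 0.2.

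**5. A milder case.** If entry is cut by 20% in one type (overall 0.90), s = 0.5/0.9 = 0.556 or 0.4/0.9 = 0.444. RR is then 1.04-1.07 or 0.93-0.96. If entry is unaffected in both types, there is no bias from this source.

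**The case against.** Four arguments carry weight.

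- **Conditioning is inherent in the question.** Recurrence after treatment can be studied only in treated women, and the plan does analyse them by assigned arm. This stands. A reader might infer that the groups compared are not the randomised arms at all, but they are selected subsets of those arms. The fault lies in the label and the missing safeguards, not in asking the question.
- **The pH mechanism is not demonstrated.** A reader might infer that the gel moves pH across the 4.7 threshold and so removes users from the diaphragm arm. The documents state buffering capacity and treat the effect on flora as something to study; they report no measured shift across 4.7. The pH criterion is a plausible second route. An effect on BV itself would be enough without it.
- **Direction and size are unknown.** A reader might infer that the bias hides a benefit or creates apparent harm. That follows only if the women kept out are assumed to be at lower risk of recurrence. Reversing that assumption produces a spurious benefit. The 25% in Aim 1 is a detectable difference in a two-sided test, for Gram-stain BV that is mostly asymptomatic, so carrying 0.75 over to symptomatic entry is a borrowed assumption.
- **Importance.** This is one aim of a single-site sub-study and does not touch the HIV endpoint. At 250 women per arm and 15% recurrence, the standard error of log RR is √[2 × 0.85/(0.15 × 250)] ≈ 0.21. The illustrated shifts (log 1.11 ≈ 0.10 to |log 0.80| ≈ 0.22) are about 0.5 to 1 standard error.

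None of this makes the label correct. The appendix itself fixes the population, the test and the label, so the conflict is not something left to an analysis plan.

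**Conclusion.** The point holds as a matter of labelling and protection. Aim 2 is not an intent-to-treat analysis under section 12.7, because its set is formed mainly after randomisation: about 390 or more of 500 women at the 5% rate, and all 660 cases in the plan's own count. Entry may depend on arm, and the unadjusted test makes no allowance for that.

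The size of any bias is not known. The range of 0.80-0.89 or 1.11-1.20 rests on the assumed risk types and on an entry ratio of 0.75, and shrinks to 0.93-0.96 or 1.04-1.07 at 0.90. It shows that a distortion worth attention beside the 33% target reduction is possible. It does not show that one will occur or which way it would run.

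**What to change.** Leave diagnosis and treatment as they are and change the analysis text in Appendix 16.1.

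1. Remove the intent-to-treat label from Aim 2 in C.2.1.2 and C.2.2.3. Describe it as a comparison by assigned arm among women treated for BV, not protected by randomisation.
2. Report the number and proportion of randomised women who enter Aim 2 from each arm.
3. Add a comparison defined in all randomised women at the site, for example treated symptomatic BV followed by Nugent-defined BV at three months, with women never diagnosed counted as free of the event. Randomisation protects this comparison, but it combines occurrence with recurrence and should be described so.
4. Adjust the among-cases comparison for baseline covariates recorded for all women at the site. Under C.1, enrolment swabs are taken only in the 500-woman BV component (500/2,200 ≈ 23% of the site), so adjustment for enrolment Nugent score can be only a sensitivity analysis there.

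Women treated before randomisation may be shown as a separate randomised subset. With about 110 women (55 per arm), two-sided power for a 33% reduction is only about 9-15% at control recurrence of 0.1-0.2.

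Dropping the three-of-three Amsel restriction from the analysis would not solve the problem, because pH remains in the diagnostic rule that decides who is treated.

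The cost is revised wording, a little more analysis and a weaker claim for recurrence. No new data collection is needed.

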**C.2.2 Sample size determination, Data Management and statistical analysis**

**C.2.2.1 Aim 1 sample size**

Based on data from other studies conducted on BV in sub-Saharan Africa, we assume that 20% of women will have BV by Gram stain at baseline, and at every visit for those enrolled in the non-intervention condom only arm. We further assume that > 80% of BV will be asymptomatic, and therefore treatment with metronidazole will have a limited effect on the overall prevalence of BV at subsequent visits. The primary outcome will be visit-specific BV prevalence. We assume that outcomes will be compared between arms on an intent to treat basis using generalized estimating equation (GEE) logistic regression model controlling for a within-participant correlation between repeated outcomes of 0.2, and that annual rates of loss to follow-up will be 5%. Based on these assumptions, 250 women per arm should be sufficient to insure 80% power to detect a  25% difference in prevalence between the two study arms as significant at the 5% level (based on a two-sided test). This corresponds to a relative risk (odds ratio) of 0.75 (0.70).

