**C.2.2.2 Aim 1 major endpoints**

Data will be analyzed in an intent-to-treat manner comparing BV prevalence at 3-monthly quarterly visits (on average women will undergo 6 follow-up visits) between arms using generalized estimating equation (GEE) logistic regression methods.

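### BV sub-study Aim 1: 250 women per arm give about 71% power on the stated inputs, not 80%; the enrolment BV result could recover part of the gap

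*Protocol*

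**What the plan says.** All the inputs to the Aim 1 calculation are in Appendix 16.1 of the Protocol:

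- **Control prevalence** (C.2.2.1): "we assume that 20% of women will have BV by Gram stain at baseline, and at every visit" in the condom-only arm.
- **Effect** (C.2.2.1): a 25% difference in prevalence, explained as "This corresponds to a relative risk (odds ratio) of 0.75 (0.70").
- **Model** (C.2.2.1): a GEE logistic regression, "controlling for a within-participant correlation between repeated outcomes of 0.2".
- **Loss** (C.2.2.1): "annual rates of loss to follow-up will be 5" per cent.
- **Test** (C.2.2.1): "significant at the 5% level (based on a two-sided test").
- **Claim** (C.2.2.1): "250 women per arm should be sufficient to insure 80% power to detect a" the stated difference.
- **Visits** (C.2.2.2): "on average women will undergo 6 follow-up visits". Specific Aim 1 in section B places them "during a 12 – 24 month follow-up after randomization", which means four to eight quarterly visits.

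Section C.1 has vaginal swabs taken at enrolment as well as every three months. The analysis descriptions in C.2.1.1, C.2.2.1 and C.2.2.2 compare follow-up visits between arms and name no baseline covariate.

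**The concern.** The plan states every number needed to reproduce its power figure, yet those numbers do not lead to 80%. Six visits per woman at correlation 0.2 carry half the information of six independent observations, and 250 women per arm then fall well short for 20% against 15%.

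This paragraph is the only justification for the 500 women in Aim 1. If the power is overstated, a null result will be taken as stronger evidence against a 25% reduction than it is. The baseline BV status of every woman is also measured, and the analysis as described does not use it, although it would give back some of the missing power at no cost.

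**Working it through.** **Inputs.** Control prevalence p1 = 0.20. Relative risk 0.75 gives p2 = 0.15; the odds ratio is (0.15/0.85)/(0.20/0.80) = 0.706, which the plan rounds to 0.70. Visits m = 6, correlation ρ = 0.2, two-sided α = 0.05, n = 250 per arm, loss 5% a year. One assumption is needed: the single stated correlation applies to every pair of visits (exchangeable).

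**Step 1, power before loss.**
- Design effect = 1 + (m − 1)ρ = 1 + 5 × 0.2 = 2.0.
- Effective observations per arm = 250 × 6 / 2.0 = 750.
- Sum of variances = 0.20 × 0.80 + 0.15 × 0.85 = 0.2875. Standard error of the difference = √(0.2875/750) = 0.01958.
- z = 0.05/0.01958 = 2.554. Power = Φ(2.554 − 1.960) = 72.4%. With the pooled variance under the null it is 72.2%, and on the log odds ratio scale 71.9%.

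**Step 2, with the stated loss.** With 5% annual loss applied visit by visit over 18 months, the average falls to 5.74 visits and the effective number to 725 per arm; power is 70.8%. Spreading planned follow-up evenly over 12–24 months gives 715 and 70.2%. A simulation with exchangeable binary data, loss and robust standard errors (6,000 replicates) gave 70.8%, and 71.0% with four to eight visits. A separate, smaller GEE simulation with loss (600 runs, standard error about 1.8 points) gave 73.7%.

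**Step 3, can 80% be reproduced?**

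| Variant (two-sided unless noted) | Before loss | With loss |
| --- | --- | --- |
| As stated, six visits | 72.2% | 70–71% |
| Odds ratio exactly 0.70 | 74.1% | 72–73% |
| Eight visits for every woman | 76.7% | 75.0% |
| One-sided 5%, six visits | 81.7% | 80–81% |

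At relative risk 0.75 without loss, 10 visits would give 79.5% and 11 would pass 80%; the schedule allows at most eight. Only the one-sided test returns the plan's figure at six visits: it needs 238 women per arm, and 238/0.95 = 251.

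**Step 4, what 80% would take.**
- Unpooled formula: 7.849 × 0.2875/0.0025 = 903 effective observations per arm, and 903 × 2/6 = 301 women. The pooled formula gives 906 and 302.
- These are before loss. Allowing for 5–7.5% loss: 302/0.95 = 318 and 302/0.925 = 327 women per arm.
- Keeping 250 per arm, the reduction detectable with 80% power is 27.3% at 750 effective observations and 27.7% at 730, so about 28% after loss.

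**Step 5, gain from the enrolment result.** Assume the 0.2 correlation also holds between enrolment and each follow-up visit. In units of the single-visit variance, the variance of a woman's mean is (1 + 5 × 0.2)/6 = 0.3333. Adjustment subtracts ρ² = 0.04, leaving 0.2933, a ratio of 0.88. Effective observations become 250/0.2933 = 852 and power 77.6% before loss, or 76.3% with about 3% of the information lost. Simulations with loss gave 76.5% with six visits and 75.6% with four to eight; a smaller run (250 replicates) gave 75.6%.

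**The case against.** The strongest objection is that the plan gives one correlation but no structure. If 0.2 applied only to adjacent visits and decayed geometrically with distance, the six-visit design effect would be about 1.40, with about 1,075 effective observations per arm. Power would then be 86% before loss and about 84–85% after it, and 250 women would suffice. A slower decay (0.2 raised to the square root of the lag) gives about 82% before loss. This is a fair reason to ask for the structure in writing. It does not rescue the stated figure: the text describes a single within-woman correlation between repeated outcomes and mentions no decay, and a common correlation is the conventional reading. Under that reading no two-sided calculation with six visits exceeds about 74%.

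The second objection is that saying nothing about a baseline covariate does not exclude one, and an analysis plan not shown could include it. That stands: adjustment is offered as a remedy, not as a separate error. It also does not reach 80% at six visits, and the gain would be smaller if correlation with enrolment fades over time.

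Third, this is one aim of a single-site sub-study, and restating a planning figure changes neither the estimate nor its confidence interval. That limits the importance, but a wrong power statement still misinforms the reading of a null result.

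**Conclusion.** The concern holds. On the plan's own inputs, with one common correlation of 0.2, 250 women per arm give 72% power before loss and about 71% with 5% annual loss for a fall from 20% to 15%. Taking the rounded odds ratio of 0.70 literally raises this to 74% at most. The chance of missing the target effect is about 29% instead of 20%.

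The close match with a one-sided 5% test suggests that the calculation was one-sided and then labelled two-sided. The HPV sub-study (Appendix 16.2, Statistical power) openly uses one-sided tests, which makes this plausible, but it remains an inference. The conclusion depends on the exchangeable reading; a decaying correlation would change it. Adjusting for enrolment BV lifts power to about 76%, provided the 0.2 correlation extends to enrolment.

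**What to change.** In Appendix 16.1, C.2.2.1:

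1. Restate the power with 250 women per arm as about 71% for a 25% relative reduction, or 80% for a reduction of about 28%. If 80% power for 25% is to be kept, the unadjusted analysis needs about 318–327 women per arm after allowing for loss (301–302 before it).
2. State the correlation structure assumed, and confirm whether the original calculation was one-sided or two-sided.
3. In C.2.2.1 and C.2.2.2, add the enrolment BV result (Nugent score or BV status) as a covariate in the GEE model, and report the power with it, about 76% under the 0.2 assumption.

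If the sample size stays at 250 per arm, the cost is a few sentences of sub-study wording and one covariate from a swab already taken, with no extra women, visits or specimens.

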**C.2.2.2 Aim 1 major endpoints**

Data will be analyzed in an intent-to-treat manner comparing BV prevalence at 3-monthly quarterly visits (on average women will undergo 6 follow-up visits) between arms using generalized estimating equation (GEE) logistic regression methods.

**C.2.2.3 Aim 2 sample size**

We assume that a minimum 5% of participants will present with symptomatic BV at every visit. Given the projected sample of 2200 women for the Zimbabwe (and a total of nearly 13,000 follow-up visits), this implies that approximately 660 diagnosed cases of symptomatic BV should be observed. The primary outcome for this aim will be recurrence of BV within three months following treatment for symptomatic disease. We assume that recurrence rates will be compared across arms on an intent-to-treat basis using a chi-squared statistic, and that loss-to-follow up rates in a three month visit cycle will not exceed 5%. Given these assumptions, and assuming three-month recurrence rates among women receiving only condoms in the range 0.1 - 0.2, a total sample size of 500 women will provide 80% power to detect a 33% reduction in recurrence associated with treatment at the 5% significance level.

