**A. Introduction**

Bacterial vaginosis, the most common bacterial genital infection in women of reproductive age has been linked to considerable gynecologic and obstetric morbidity. Recent studies demonstrate that BV may be a cofactor in acquisition of human immunodeficiency virus type (HIV) infection. 1-3. The highest prevalence of BV has been in sub-Saharan Africa where HIV infection is also common 2,3. It has been postulated that BV may increase susceptibility to HIV infection by a variety of mechanisms including possibly altering the host’s defense system through the absence of the normal H2O2-producing vaginal lactobacillus (which allow to maintain the natural acidic pH of the vagina), with loss of the protective myeloperoxidase halide-hydrogen peroxide system 4, and by production of metabolic by-products that may increase HIV replication 5,6 or activate target cells for HIV infection 7. If any of these hypotheses are correct, reduction of BV prevalence could significantly reduce female HIV acquisition. The high prevalence of BV in sub-Saharan Africa remains unexplained. Though considerable evidence supports sexual transmission of BV, factors like clothing, climate and hygiene may influence vaginal flora. Of the various risk factors associated with BV, the contribution of each to causing BV may vary depending on hygienic, sexual and other practices 8. BV treatment with metronidazole was first found to be to be effective in the initial clearing of symptoms and signs of BV 9, but has since proven disappointing even in industrialized countries, since recurrence rates reach 40% within 3 to 6 months after treatment with oral or intravaginal medication 10,11.In Uganda, administration of metronidazole, azithromycin and ciprofloxacin to large populations of adults of reproductive age every 10-months did not reduce the prevalence of BV below 50% 12.

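### BV sub-study Aim 2: 500 women in total give about 25–49% power (two-sided) for the planned 33% reduction, not the stated 80%

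*Protocol*

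**What the plan says.** Appendix 16.1, section C.2.2.3, sets out the design of Aim 2. The outcome is BV recurrence within three months of treatment for symptomatic disease. The arms are compared by intent to treat with a chi-squared statistic, and at most 5% of women are lost in a three-month cycle. The control rate is given as "assuming three-month recurrence rates among women receiving only condoms in the range 0.1 - 0.2". The conclusion is that "a total sample size of 500 women will provide 80% power to detect a 33% reduction in recurrence" at the 5% level. Section C.1 repeats the number: "500 women with symptomatic BV will be required".

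Aim 2 does not say whether the test is one- or two-sided. Aim 1 of the same appendix (C.2.2.1) is explicitly two-sided.

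On the supply of cases, Aim 2 says "We assume that a minimum 5% of participants will present with symptomatic BV at every visit" and projects about 660 symptomatic cases from 2,200 Zimbabwean participants. Aim 1 takes BV prevalence as 20% at every visit in the condom-only arm and adds: "We further assume that > 80% of BV will be asymptomatic".

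**The concern.** A one-third reduction from a rate of 10% or 20% is an absolute difference of only 3.3 or 6.6 percentage points. Two groups of 250 are small for differences of that size, so 80% power looks too high on sight.

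Recurrence after treatment is one of the sub-study's two specific aims. If the power statement is wrong, a null result would be read as coming from a comparison with an 80% chance of finding the effect, when the real chance was much lower. That could lead readers to dismiss an effect the sub-study had little chance of detecting.

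**Working it through.** **Inputs, all from C.2.2.3 unless noted**
- 500 women in total, taken as 250 per arm (the main trial allocates 1:1); about 237 per arm after 5% loss.
- Control recurrence p1 = 0.10 to 0.20.
- 33% reduction, so p2 = 0.67 × p1: 0.067 or 0.134.
- 5% level, chi-squared test of two proportions. Two-sided is an assumption taken from Aim 1.

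**Formula**

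Power = Φ{ [ (p1 − p2)·√n − z·√(2·p̄·(1 − p̄)) ] / √( p1(1 − p1) + p2(1 − p2) ) }, with n per arm, p̄ the mean of p1 and p2, and z = 1.96 (two-sided 5%).

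**Control 0.20, n = 237**
- (p1 − p2)·√n = 0.066 × 15.395 = 1.016
- z·√(2 × 0.167 × 0.833) = 1.96 × 0.5275 = 1.034
- √(0.1600 + 0.1160) = 0.5254
- Power = Φ(−0.034) = 0.487

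**Control 0.10, n = 237**
- 0.033 × 15.395 = 0.508
- 1.96 × √(2 × 0.0835 × 0.9165) = 0.767
- √(0.0900 + 0.0625) = 0.3905
- Power = Φ(−0.663) = 0.254

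**Across the stated range**

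| Control rate | Two-sided, 250 per arm | Two-sided, 237 per arm | One-sided, 250 per arm | One-sided, 237 per arm |
|---|---|---|---|---|
| 0.10 | 26.5% | 25.4% | 37.8% | 36.4% |
| 0.15 | 38.6% | 37.0% | 51.1% | 49.3% |
| 0.20 | 50.7% | 48.7% | 63.1% | 61.1% |

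**Attempts to reproduce 80%**
- A reduction of exactly one third (ratio 0.667) gives 25.8% and 49.5% with 237 per arm.
- Unpooled-variance and arcsine formulas give 27% to 51% (two-sided, 250 per arm).
- Reading the 33% as an odds ratio of 0.67 gives 23% to 39%; an events-based (Schoenfeld) calculation gives 25% to 45%. Both are two-sided with 250 per arm.
- Using all 660 projected cases, 330 per arm with no loss, gives 33% to 62% (two-sided).
- Taking 500 as the number **per arm** gives 80.0% at control 0.20 before loss, but 47% at control 0.10.

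Only the last reading reaches the stated figure, and only at the upper end of the range.

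**What 80% power would need (two-sided)**

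n per arm = [ 1.96·√(2·p̄·(1 − p̄)) + 0.842·√( p1(1 − p1) + p2(1 − p2) ) ]² / (p1 − p2)²
- Control 0.20: (1.034 + 0.442)² / 0.066² gives 501 per arm, 1,002 in total, or 1,055 after dividing by 0.95.
- Control 0.10: (0.767 + 0.329)² / 0.033² gives 1,102 per arm, 2,204 in total, or 2,320 after dividing by 0.95.
- With 237 per arm, the smallest reduction detectable with 80% power is about 65% at control 0.10 and 46% at control 0.20.

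**Symptomatic-BV assumption (secondary)**
- Aim 1: 20% prevalence with more than 80% asymptomatic leaves less than 0.20 × 0.20 = 4% symptomatic per visit.
- Aim 2: at least 5% per visit; 0.05 × 2,200 × 6 visits = 660. At 4% the same product is 528.

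**The case against.** **Sidedness.** The strongest objection is that Aim 2 does not specify a two-sided test, and two other appendices in this protocol (the HPV and PSA studies) plan one-sided tests. That is fair: the 25–49% range rests on an assumption. It does not rescue the claim, because one-sided power is at most 63% even before losses.

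**The 5% versus 4%.** Aim 1's 20% is BV by Gram stain. Aim 2's 5% is symptomatic BV presenting at visits, first diagnosed by modified Amsel criteria. These are different case definitions, so 4% is not a strict ceiling on the second. A reader might infer a flat contradiction, or a supply below 500, but the documents do not establish either: 528 projected episodes still exceeds 500, and the site target was later raised to 2,500 (0.04 × 2,500 × 6 = 600). What stands is a request to reconcile the two assumptions.

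**Other readings that go too far**
- A reader might infer that the chi-squared test would treat 660 visit-level episodes as independent women. The planned sample is 500 women; the 660 is the projected supply. How repeat episodes are handled can be left to the analysis plan.
- A reader might infer that requiring all three Amsel criteria shrinks the sample. The initial diagnosis in C.1 already uses those three criteria, so this may remove nobody. The added Nugent requirement could remove some women, but no figure is given.
- A reader might say the power is adequate because the appendix introduction cites that "recurrence rates reach 40% within 3 to 6 months after treatment with oral or intravaginal medication". At a control rate of 40%, 500 women would give about 86–88% power. But that is a rate reached over three to six months, whereas the endpoint is at three months and C.2.2.3 fixes 0.1–0.2. Adopting 40% because it restores the power would be back-fitting.

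**Conclusion.** The power statement is wrong as written. On the protocol's own inputs, 500 women in total give about 25% power at control recurrence 0.10 and 49% at 0.20 after 5% loss (27% and 51% before loss), assuming a two-sided 5% test and equal arms. On that basis a true 33% reduction would be missed about half to three-quarters of the time. With a one-sided test it would be missed in about 39% to 64% of cases after loss.

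That 500 is a per-arm number reported as a total is a plausible explanation, since 501 per arm is the requirement at control 0.20. It remains an inference that the protocol does not confirm, and it would still leave the claim false at the lower end of the range.

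The error concerns the second aim of a single-site sub-study. It does not touch the HIV primary endpoint, the main trial's sample size or its interim monitoring. It should be corrected, but it does not rank with errors that threaten the main trial.

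**What to change.** In C.2.2.3:
1. Replace the 80% claim with the actual power for a 33% reduction (about 25% to 49%, two-sided, after 5% loss), or with the reductions detectable at 80% power (about 65% at control 0.10 and 46% at 0.20).
2. State whether the test is one- or two-sided. If it is one-sided, quote 36% to 61% after loss instead.
3. If the 0.1–0.2 assumption stands, describe Aim 2 as exploratory, and carry the same wording into C.1 where the 500 is repeated.
4. Reconcile the 5% symptomatic-BV assumption with Aim 1's 20% prevalence and more than 80% asymptomatic, for example by stating which case definition each figure refers to.

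The cost is a text change to one appendix. No main-trial procedure, visit or sample size changes. The price is a less favourable, but correct, power statement.
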